### Medication Withdrawal Procedures

In both studies, depending on the type of medication and, hence, its half-life, patients will withdraw from their medication for a maximum of 48 h prior to their off-medication assessments. Specifically, extended-release drugs: Mirapex extended release, Requip extended release and Neupro patches will be stopped 48 h prior to evaluations. Regular Mirapex, regular Requip, Sinement sustained or extended release and Rytary are stopped 24 h prior to off evaluations. Sinement immediate release, Comtan, Stalevo, Amantadine, Azilect, Selegiline, and Artane are stopped 12 h prior to off-medication evaluations.

### Adverse/Serious Events Reporting From the Vibrotactile Device

There are no formal statistics available on the vibrotactile stimulator's safety. Previous pre-clinical study patients have reported the glove as being tolerable with little to no side effects (17). There may be physical discomfort (e.g., pinching, numbing, skin indentations, etc.) associated with wearing the vibrotactile glove and study personnel will be vigilant for this unlikely possibility. In a previous study (17), patients reported a decrease in their medication over the course of vCR treatment. With this in mind, we hypothesize that PD patients with medication-induced dyskinesias might experience an increase of the medication-induced dyskinesias as vCR stimulation reduces the required medication dose, and as a result, patients may want to decrease their medication. If patients experience dyskinesia from the vibrotactile device, they are instructed to consult their neurologist about potential medication decreases and to not decrease their medication without consulting their doctor first. If patients and their neurologists decide to decrease their medication, patients are instructed to contact the study's treating movement disorders neurologist no later than 10 business days since medication changes. If in the event the patient experiences clinical worsening from the vibrotactile device, the patient is instructed to contact the study's treating movement disorders neurologist no later than 10 business days from the time of the event.

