### Study Personnel and Their Roles

This study will include five movement disorders neurologists who are blinded during the first study. The first movement disorders specialist will serve as the *treating movement disorders neurologist* and perform physical and neurological examinations, evaluate and provide medical advice regarding patients' medication intake and serve as point of contact in the event of a serious or adverse event either unrelated or related to vCR for both the first and second study. The second movement disorders neurologist will serve as the studies' *main MDS-UPDRS movement disorders evaluator* who will perform assessments on patients throughout the first and second study. Three other movement disorders specialists will serve as the study's *video MDS-UPDRS III raters* for the first (main) study. The clinical research coordinators will oversee consent, objective motor measurements, video recordings, patient contact, vibrotactile glove administration, EEG recordings, voice recordings, and all self-report tests and questionnaires in both studies. Speech analysis will be performed by a voice disorders specialist and her trained team. An un-blinded statistical analyst, who is not associated with the study team and does not report to any member of the study team, will perform all statistical tests on outcome measures. All movement disorders specialists, speech analysis, and clinical research coordinators, will be blinded until completion of the first study.

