#### Study 1: At Home Therapy Procedures

During the first study visit, patients will be taught how to use, wear and adjust the vibrotactile device. Patients will then be sent home and asked to stimulate for a total of 4 h a day with a break in between each 2-h session (minimum 1-h break) for 6 months. At the end of the 6 months, patients will be asked to stop stimulation for 1 month. During the 7-month study, patients are asked to continue their prescribed medication as needed. If the patient would like to decrease his or her medication due to positive motor results throughout the study, the patient can reduce medication according to the advice of our study's treating movement disorders neurologist and the patient's personal movement disorders neurologist. While at home, patients will have their own Kinesia ONE system to log medication information and perform motor tasks while on medication 1–3 times every week to monitor movement ability. After the start of the study, patients will have a 1-month checkup with the study's treating movement disorders neurologist over the phone to check in on how the participant is doing. If the participant experiences any worsening of motor ability/or side effects that he/she believes is due to the vibrotactile device after the 1-month checkup, the patient can schedule a phone call with the study's treating movement disorders neurologist to discuss what the next steps will be. In the event the participant experiences an adverse event or a serious adverse event either related or unrelated to glove, he/she is required to schedule a call with the study's treating movement disorders neurologist for evaluation within 3 days of the event. For a detailed schematic of study 1 events see Figure 3.

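### Two reporting deadlines can apply to the same device-related adverse event: 3 days in the Study 1 at-home procedures, 10 business days in the safety-reporting section

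*Protocol article*

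**What the plan says.** All the statements are in the protocol article.

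- **Study 1: At Home Therapy Procedures, mandatory call.** The trigger and duty read: "an adverse event or a serious adverse event either related or unrelated to glove, he/she is required to schedule a call". The time limit follows: the patient is "required to schedule a call with the study's treating movement disorders neurologist for evaluation within 3 days of the event".
- **Same section, the sentence before, optional call.** One trigger is "any worsening of motor ability/or side effects that he/she believes is due to the vibrotactile device", if it arises later than the planned phone check at 1 month. The response offered is that "the patient can schedule a phone call with the study's treating movement disorders neurologist to discuss what the next steps will be". No time limit is attached.
- **Adverse/Serious Events Reporting From the Vibrotactile Device.** Where the glove causes clinical worsening, the rule is that "the patient is instructed to contact the study's treating movement disorders neurologist no later than 10 business days from the time of the event". The sentence is not restricted to Study 1 or Study 2.
- **Same section, medication decreases.** Patients are also told "to contact the study's treating movement disorders neurologist no later than 10 business days since medication changes". This has a different trigger and is not part of the conflict.
- **Study Personnel and Their Roles.** The treating neurologist is the contact "in the event of a serious or adverse event either unrelated or related to vCR for both the first and second study".
- **Remote Study Procedures (Study 2).** No deadline for reporting adverse events is given.

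**The concern.** The 3-day rule covers every adverse event and names glove-related ones expressly. The 10-business-day rule covers clinical worsening caused by the glove. The article does not define either term against the other, does not exclude adverse events from the second rule, and does not say which rule prevails. A glove-related worsening that is an adverse event therefore carries two deadlines, both owed to the same physician.

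The patient starts these reports from home, so the patient's understanding of the deadline decides when the physician hears of the event. The device is investigational, and the reporting section itself says that no formal safety statistics exist for it. That section also foresees one kind of device-related worsening, an increase in dyskinesia. At stake is delay in safety review, not the efficacy comparison.

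**Working it through.** The plan gives no statistical figure to reproduce. The check sets the rules side by side and then counts days.

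**Step 1: compare the rules**

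| | At-home section, mandatory call | At-home section, optional call | Reporting section |
|---|---|---|---|
| Trigger | Any adverse or serious adverse event, glove-related or not | Motor worsening or side effects the patient attributes to the device, after the 1-month checkup | Clinical worsening from the device |
| Duty | Required | Available | Instructed |
| Limit | 3 days | None | 10 business days |
| Contact | Treating neurologist | Treating neurologist | Treating neurologist |
| Scope | Study 1 | Study 1 | Not limited to one study |

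**Step 2: find the overlap.** The first and third columns both apply when a worsening (a) comes from the device and (b) is an adverse event. The first column includes glove-related events by its own words. The third excludes nothing on grounds of type or seriousness. The overlap is therefore not empty on the text.

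**Step 3: size the gap.** Assumptions: the event day is not counted, there are no public holidays, and the 3 days are calendar days.

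Gap = (calendar days to the 10th business day) − 3

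| Day of event | 10 business days, in calendar days | Gap | Ratio to 3 days |
|---|---|---|---|
| Monday to Friday | 14 | 14 − 3 = 11 | 14/3 = 4.7 |
| Saturday | 13 | 13 − 3 = 10 | 13/3 = 4.3 |
| Sunday | 12 | 12 − 3 = 9 | 12/3 = 4.0 |

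**Step 4: vary the calendar-day assumption.** If the 3 days were meant as business days, they would be 3 calendar days from a Monday, Tuesday or Sunday event, 4 from a Saturday and 5 from a Wednesday to Friday. The gaps become 14 − 3 = 11 (Monday, Tuesday), 14 − 5 = 9 (Wednesday to Friday), 13 − 4 = 9 (Saturday) and 12 − 3 = 9 (Sunday). The range is again 9 to 11 days.

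**Step 5: Study 2.** The 3-day rule sits under the Study 1 procedures and the remote procedures set no limit. For device-related worsening in Study 2, the reporting section's 10 business days is thus the only deadline the article states, even if the worsening is an adverse event.

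**The case against.** **Two tiers may be intended.** The at-home section puts lesser worsening and adverse events in consecutive sentences with different duties, which suggests the authors saw two categories. Clinical worsening resembles the first. This reading is reasonable, and it is why the conflict is conditional: the deadlines clash only where the worsening is also an adverse event. It does not remove the conflict, because the article never draws the line between the tiers and the 3-day rule expressly takes in glove-related events.

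**The section heading proves little.** The reporting section is headed as dealing with adverse and serious events, but it also contains glove discomfort and notification of medication decreases, which are not all adverse events. That is fair. The heading does not show that all worsening mentioned there is an adverse event; the point needs only that none of the text excludes it.

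**The limits are nested.** A call within 3 days meets every rule, so no patient faces duties that cannot all be met. This stands. The difficulty is confined to the patient who uses the time the longer limit allows.

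Three stronger readings might be inferred and are not supported:

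- *That the optional call is a third conflicting instruction.* An offer of a call is compatible with an outer limit for contact set elsewhere. It is at most unclear beside the other two.
- *That serious worsening in Study 1 may wait 10 business days.* The 3-day rule names serious adverse events, and the reporting section does not claim to override it.
- *That the gap means extra stimulation.* Patients are "asked to stimulate for a total of 4 h a day with a break in between each 2-h session", so 9 to 11 days would be 9 × 4 = 36 to 11 × 4 = 44 hours. That assumes continued use of a device the patient believes is harmful, although the controller can be paused or switched off (Vibrotactile Device Description). The article links no harm to those hours, and Study 2 allows at most 2 h a day.

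**Conclusion.** The point holds in a conditional form. For clinical worsening from the device that is also an adverse event, the article states two deadlines to the same neurologist. A patient who relies on the longer one may report 9 to 11 calendar days late against the shorter one, in a window 4.0 to 4.7 times as long. These are permitted maxima, not expected delays. Home Kinesia ONE sessions 1 to 3 times a week, medication reports and the tolerability questionnaires may reveal some worsening sooner, but the article does not offer them in place of the call.

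The size rests on no public holidays, the event day not being counted, and 3 calendar days running to the call itself; the wording could instead tie the 3 days to the neurologist's evaluation. The conflict between two stated rules is within Study 1; in Study 2 the longer limit is the only one stated. The primary outcome, its analysis and the sample size are not affected. This is an error in stated rules rather than detail left to a fuller document. It should be fixed because it concerns safety reporting and the repair is cheap. Confidence is medium, since the patient instructions actually issued are not shown and may already separate the categories.

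**What to change.** In Adverse/Serious Events Reporting From the Vibrotactile Device, state that clinical worsening from the device which is an adverse or serious adverse event follows the 3-day rule of Study 1: At Home Therapy Procedures, in both Study 1 and Study 2. Keep 10 business days only for notifying medication decreases and for worsening that is not an adverse event. Optionally, add to the at-home section that the call offered for perceived worsening or side effects does not replace the mandatory call. Bring the patient instructions into line.

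The drafting cost is about one sentence, one optional clause and the matching patient instruction. The operational cost is some additional early calls, including for worsening that proves to be ordinary disease progression, to a neurologist whose role is already in place. The change also sets an explicit 3-day limit in Study 2, where the remote procedures state none; that is a new obligation and should be adopted knowingly. Limiting the change to worsening that is an adverse event avoids a 3-day call for every perceived decline in a progressive disease.

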### Standard Operating Procedures and Training

For all evaluations, standard operating procedures (SOPs) have been developed to ensure uniformity between all study personnel. All study personnel received training of all protocol practices and use of equipment for their protocol roles.

## Discussion

This paper describes the study procedures for the study *Vibrotactile coordinated reset: a non-invasive treatment for Parkinson's disease*. This study is comprised of two types of study protocols which include Study 1, main phase double-blind sham-controlled study, and Study 2, second phase, remote dosing regimen within the same study participants who all receive active vCR. In both studies, vCR therapeutic benefits are examined by implementing motor and non-motor evaluations.

### Study 1

Testing vCR against a dedicated sham group will further assist in the true understanding of vCR's therapeutic motor benefits. A larger sample size may additionally aid in how vCR affects sub-motor types of PD, for example, tremor-dominant (TD), postural instability and gait difficulty dominant (PIGD-GD) and akinetic rigid types.

Non-motor related questionnaires and examinations such as sleep and smell have not yet been systematically studied in vCR experiments. Olfactory loss is commonly reported in PD patients, with some studies reporting ≥ 90% of patients with smell deficits (39, 40). The olfactory system is distinct, in that it has the unique capability to be activated by sniffing which by definition is a sensorimotor ability (41). Therefore, a therapy modulating sensorimotor areas of the brain (17) may have a positive impact on olfactory ability. Sleep disturbances are frequently reported in PD patients (42). Causes of sleep disturbances have been associated with nocturnal motor symptoms and dopaminergic medication (43). Given that vCR has positive benefits on the motor system and allows for a reduction of dopaminergic medications (17), we expect sleep to improve with vCR treatment. Speech and voice abnormalities are another area of interest simply because dopaminergic medication has been known to cause dysfluent speech (44–46) and traditional DBS can cause worsening of voice and speech (11). While the cause of voice and speech abnormalities is poorly understood, it is believed that improper integration of sensory and motor inputs due to dopamine loss within the striatum and basal ganglia can result in motor deficits that negatively affect subsystems related to speech motor control (47). Numerous studies have documented PD speech abnormalities related to sensorimotor deficits including errors in kinesthetic measurements (48), problems involving orofacial perception (49), and difficulties incorporating proprioceptive information during movement (50). Therefore, a therapy that targets the sensory and motor system and its interactions may have a positive benefit on speech and voice abnormalities in PD.

Using possible techniques such as the VTDT may aid in the understanding of vibratory sensory differences or abnormalities on a per patient basis which could help modify vCR patterns and parameters. Specifically, time as a dependent measure signifying the patient's vibratory temporal discrimination threshold may correlate to vCR effects. These measurements can then be used to modify vCR parameters on an individual basis so that patients receive the maximal benefit from vCR therapy. This could ultimately lead to a calibration-based personalized vCR therapy. Our VTDT is motivated by studies exploring somatosensory temporal discrimination in PD patients (51, 52). For instance, Conte et al. (51) used paired electrical stimuli delivered through surface skin electrodes. They found that somatosensory temporal discrimination threshold values were significantly greater in PD patients compared to in healthy subjects. In PD patients, dopamine reduced (i.e., partially restored) somatosensory temporal discrimination thresholds, whereas DBS delivered to the STN further degraded (i.e., increased) somatosensory temporal discrimination thresholds (51). In our pilot studies, we observed that in the course of the vCR therapy PD patients needed less dopaminergic medication (17). Accordingly, we hypothesize that vCR therapy may cause a cumulative and long-lasting reduction of somatosensory temporal discrimination thresholds assessed off medication.

In our VTDT, we deliver two vibratory bursts to the index and the middle finger. This is because the goal of vCR therapy is to reduce abnormal synaptic connectivity. We hypothesize that due to vCR treatment, unwanted synaptic connectivity and, hence, abnormally strong interactions between index and middle finger decrease so that sensory input from index and middle finger can be processed in a separated and, thus, more efficient manner. Effective CR stimulation requires that the overlap of stimulated neuronal sub-populations should not attain higher levels (17, 23, 53). Hence, there might be an intricate relationship between the vibration amplitude used for vCR and treatment outcome. For instance, the stronger the abnormal synaptic connectivity between neighboring fingers, the smaller the vibration amplitude should be. However, particularly weak vCR may be less effective since the desired vibration phase-locked neuronal activity may occur in only smaller portions of the sensory thalamus and the sensorimotor cortex [see (16, 17)]. Hence, vCR stimulation might be more favorable if delivered at vibration amplitudes adapted to the VTDT results. Accordingly, during the course of vCR treatment the optimal vibration amplitude might need to adapt using VTDT results. However, this remains to be shown, e.g., in a first step by correlating VTDT and therapeutic outcome.

Patients with PD suffer from impairments in sensorimotor integration (48, 54–56). EEG recordings specifically investigating sensorimotor activity are important in understanding how the sensory system interacts with the motor system in PD. Vibration alone activates cortical motor areas of the brain (27), with desynchronization of the alpha and beta band corresponding to increased sensorimotor activity (27, 28). Faster (button press) times to a visual cue have been associated with desynchronization of sensorimotor rhythm (SMR) within the beta band, while increases of SMR are associated with longer reaction times (57). In our previous study, we found that after 3 months of vCR treatment, PD patients displayed a decrease in high beta band power over the sensorimotor cortex while patients were at rest (17). Based on this finding, we expect to find similar decreases in beta band power in response to a vibratory cue. In addition, reduction in reaction times accompanied by reduced beta power activity over the sensorimotor cortex during the course of vCR treatment could serve as a possible indicator of increased sensorimotor integration.

The readiness potential (RP) is an event related potential (ERP) slow wave that begins 1–2 s preceding voluntary movement (58). The RP contains early and late components, with the early component reflecting preparation of movement and the later component related to motor execution (58). The early RP is thought to be generated from the supplementary motor area (SMA) while the late readiness potential is associated with activation of the primary motor cortex (59). Dysfunction of the SMA (60, 61) and lower amplitudes of the RP have been found in PD patients (62–65). For this study, increases in RP amplitude prior to button press during the course of vCR treatment could serve as an indicator of improvements in motor ability and SMA function. In addition, Contingent Negative Variation (CNV) is a slow wave cortical potential that is related to attention, expectancy, and motor preparation (66, 67). It occurs when a participant is presented with a cued stimulus (i.e., vibration or sound) that requires a motor response (59, 67). Patients with PD exhibit reduced CNV amplitude (65, 68). Increases in CNV amplitude could serve as a measure of improved preparation and execution of a motor response in PD patients treated with vCR.

### Study 2

### Summary and Outlook

Our study protocol comprises two study phases: *Study 1* is a double blinded randomized sham-controlled proof-of-concept study which corresponds to a phase IIA trial of the pharmaceutical trial categorization (70). The goal of this study is to demonstrate clinical efficacy of vCR compared to sham stimulation. To ensure therapeutic dosage, in study 1 we will apply two times 2 h of vCR or sham stimulation per day, respectively. However, in one patient of our case studies, in total 2 h vCR per day were sufficient to cause pronounced therapeutic effects (17), indicating that a daily dose of 4 h may not be necessary.

*Study 2* aims to obtain knowledge of the therapeutic benefits of vCR stimulation at a reduced dosage regimen. To this end, sham patients from study 1 will be crossed over into active vCR for study 2, totaling 30 active patients for the dose finding study 2. All patients in study 2 will receive vCR at a dose ranging from 2 h a day (maximum daily dose) to 2 h a day three times a week (minimum weekly dose) for 6 months. Patients will select their actual weekly dose within this reduced dosage range depending on their individual needs, supposedly requiring less compliance and causing less interference with patients' day-to-day activities. Study 2 serves three purposes: (i) In the patients who received vCR in study 1, study 2 enables to collect data regarding safety, tolerability, and efficacy on a longer time scale by delivering vCR for in total 12 months instead of 6. (ii) Comparing the effects obtained in vCR patients in study 1 with the effects observed in the sham patients from study 1 crossing over to low-dose vCR in study 2 provides a dose finding comparison between low-dose and high-dose 6-month vCR therapy, similar to a phase IIB trial in terms of the pharmaceutical trial categories (70). (iii) In addition, in both patient groups (i.e., vCR vs. sham patients from study 1) therapeutic effects obtained in study 2 will be separately correlated with the integral amount of self-administered dose.

Depending on the results of studies 1 and 2, additional dose finding studies might be envisioned to further optimize and potentially reduce the dosing pattern as well as to further optimize the stimulation pattern, e.g., by increasing the temporal jitter of stimulus onsets used for noisy vCR (17).

